## Abstract

**Background:**

Globally, around 800,000 people die by suicide annually, with 77% of these deaths occurring in low- and middle-income countries. Suicidal ideation, frequently observed among adolescents, is directly linked to suicide attempts. Pakistan has witnessed a marked escalation in suicide rates in recent years, with Gilgit-Baltistan (GB) reporting the highest incidence. Extensive research indicates that tailored suicide prevention strategies can mitigate suicidal ideation, attempts, and related fatalities.

**Objective:**

This study aims to validate and evaluate the efficacy of suicide prevention programs, RAAHI (the guide) and safeTALK, tailored to the cultural and social context of GB, Pakistan, in preventing suicidal ideation and improving the mental well-being of school-going adolescents.

**Methods:**

The investigation will assess the efficacy of the RAAHI intervention among 267 adolescents across 4 private schools in GB using an interrupted time-series design with a pre-post test framework. The first intervention, RAAHI, a suicide literacy module, is designed to empower participants with the knowledge and skills to recognize signs of suicidal ideation, engage them empathetically, and connect individuals in crisis with appropriate support. The second intervention, safeTALK, a 4-hour educational workshop, incorporates presentations, videos, discussions, and interactive sessions to teach participants the tell, ask, listen, and keep safe steps. Outcome measures include changes in knowledge, confidence, willingness to intervene, and help-seeking behaviors, analyzed using descriptive statistics, 2-tailed paired *t* tests, and ANOVA. Ethics approval was granted by the Aga Khan University Ethics Review Committee (2023-8509-24844).

**Results:**

As of April 2025, 267 participants have been recruited from 2 of the 4 schools; data collection commenced in March 2025 and is projected to conclude in August 2025. Final results are expected to be published by February 2026.

**Conclusions:**

This study will offer critical insights into the adaptation and effectiveness of the RAAHI suicide prevention intervention in a low-resource, culturally specific setting. The findings are anticipated to inform scalable suicide prevention initiatives in school settings across Pakistan and similar low- and middle-income contexts, ultimately contributing to reduced suicidal ideation and attempts among adolescents.

**International Registered Report Identifier (IRRID):**

DERR1-10.2196/67193

## Introduction

### Background

Suicide is a notable global public health concern, resulting in a staggering number of fatalities annually [1]. It ranks among the 5 leading causes of death, representing more than one-third of all fatalities [2]. The rising global suicide rate, surpassing 800,000 deaths annually, underscores the urgency of addressing this critical public health concern [3]. In Australia, suicide is the leading cause of death among individuals aged between 15 and 24 years, with an annual rate of 11.6 deaths per 100,000 population [4]. Moreover, each suicide case potentially corresponds with more than 20 attempted suicides, emphasizing the urgent need for suicide prevention interventions. The World Health Organization [3] suggests an alarmingly high prevalence of suicidal ideation, encompassing nonfatal suicide attempts and self-harm. This tragic occurrence is widespread across the globe, with 77% of suicides taking place in low- and middle-income countries (LMICs) [2].

In addition, on a global scale, suicide ranks as the fourth leading cause of death for adolescents and young adults aged between 15 and 29 years [5]. Over the past 5 years, the United Arab Emirates has recorded the highest rate of suicides globally (11.4%), followed by the United Kingdom (10.80%), Nepal (10.33%), the United States (8.9%), and Pakistan (7%) [6]. Within the spectrum of mental health disorders, suicide emerges as the foremost cause of violent death, even among the economically active age group of people aged between 15 and 44 years [6]. According to a meta-analysis, 22.3% of college students at some point in their lives had suicidal thoughts, plans or made attempts [7]. In addition, a survey of 8113 high school students in Hawaii found that 16.4% of the adolescents reported having suicidal thoughts, and nearly 10% acknowledged having attempted suicide at least once in their lives [8].

Adolescents are highly susceptible to mental health problems due to academic stress, interpersonal issues, and the transition to adulthood; all of these factors exert substantial influence on their physical, emotional, social, and mental well-being [9]. In Pakistan, these challenges are exacerbated by social and cultural pressures, mental health being considered a stigma, and limited access to treatment, which impacts social functioning and academic success, with long-term consequences [10]. Evidence indicates that adolescents susceptible to self-harm often refrain from seeking support from parents or professionals; instead, they turn to their peers for assistance [11], who, due to their limited experience and knowledge, are usually not able to provide the required assistance.

Mental well-being signifies flourishing across emotional, psychological, and social domains, characterized by satisfaction, resilience against adversity, a sense of purpose, positive feelings, and the capacity for meaningful connections and activities [12]. Given the significance of mental well-being for adolescents and the concerning prevalence of mental disorders within this demographic, prioritizing mental health interventions tailored to address the unique needs and concerns of this demographic is essential due to the high burden of mental disorders prevailing in this age group [13]. Numerous suicide prevention programs aim at enhancing skills in identifying and supporting individuals at risk while also improving their self-efficacy, mental health literacy, and attitudes [14]. The enhancement of self-efficacy and mental health knowledge is linked to increased resilience in youth, fostering a sense of control, thereby significantly reducing the likelihood of engaging in suicidal ideation [15].

Increasing evidence suggests that school-based suicide prevention interventions are effective in their approach [11]. Such interventions span various levels of prevention, encompassing primary efforts, such as public awareness campaigns; secondary approaches, such as gatekeeper training programs; and tertiary interventions, such as psychotherapy and postvention strategies, including survivor support groups. Similarly, expanding the conventional classification of mental health interventions, suicide prevention strategies can be categorized into universal (targeting the public) or selective (aimed at specific high-risk groups with elevated lifetime risk, such as adolescent and psychiatric inpatients) [16].

A systematic review of 13 randomized controlled trials (RCTs) reported that the risk of suicide-related behavior among youth exposed to an educational intervention was 0.31 times lower compared to those in the unexposed group [17]. Similarly, another review of 14 studies assessing the impact of school-based gatekeeper training revealed enhancements in gatekeepers’ knowledge, attitudes, self-efficacy, and inclination to intervene [18]. An RCT of the Signs of Suicide program showed a decrease in suicide attempts over a 3-month period [19]. Moreover, a large-scale RCT of a Youth Aware of Mental health program, involving more than 11,110 secondary school students across 10 European countries, revealed a 55% reduction in incidents of suicide attempts and a 50% decrease in severe suicidal ideation compared to control groups at 12 months after intervention [20].

In Australia, a crucial component of the integrated, regionally based approach to suicide prevention was gatekeeper training, which was widely implemented as a universal approach in secondary schools. Such training programs aim to equip students with skills to serve as peer gatekeepers, capable of identifying suicide warning signs, addressing concerns, and facilitating appropriate referrals for assistance and care [18,21].

safeTALK, a gatekeeper training initiative, seeks to elevate awareness regarding suicide prevention by framing it as a collective community responsibility, envisioning a helping role for every individual [22]. In addition, it empowers individuals without professional mental health backgrounds to confidently and effectively support someone showing signs of emotional distress. Studies have shown that this training enhances the effectiveness of informal mental health support for those experiencing emotional imbalance [2].

Pakistan, located in Southeast Asia, grapples with numerous health and social challenges due to persistent waves of violence, political instability, and recurrent changes in the social infrastructure, which have significantly increased the burden of physical and mental ailments impacting individuals of all ages [23]. Unfortunately, Pakistan lacks accurate statistics on suicide deaths and suicidal attempts [24] due to underreporting of such cases, which happens because of social factors, particularly the stigma attached to such cases. However, recently published studies provide some insights into suicide deaths in Pakistan, where adolescents exhibited suicidal ideation and attempted suicide at the rates of 40% and 7%, respectively [25]. Moreover, in 2019, suicide mortality rates in Pakistan were estimated to be 8.9 per 100,000 population [26,27]. Gilgit-Baltistan (GB), comprising valleys located among the snow-clad mountains of northern Pakistan, has shown an alarming increase in adolescent mental health issues, including suicidal ideation and suicide rates, which has been particularly exacerbated during and following the COVID-19 pandemic [28].

To address the rising trend of suicidal ideations and attempts, prevention initiatives, such as the safeTALK program, hold significance, as they can help in disseminating awareness and education among adolescents through suicide literacy. Programs such as these aim to cultivate courage and confidence among adolescents to openly discuss suicidal thoughts and ideations and encourage help-seeking behaviors to approach professionals, such as psychologists or counselors. Extensive evidence supports the efficacy of the safeTALK program, which has been successfully implemented in various countries [29]. However, Pakistan, with its unique cultural and social setup, has yet to conduct a comprehensive analysis of the effectiveness of such programs.

The RAAHI suicide prevention program for school-going adolescents in GB was based on the theoretical frameworks of mental health literacy and resilience theory. Mental health literacy refers to the information and views about mental disorders that help with their detection, care, and prevention [30]. Improving mental health literacy enables people to recognize indicators of mental distress, cultivates good attitudes about getting help, and raises awareness of available support resources. By including mental health literacy in our program, we hope to provide teenagers with the tools to recognize and treat mental health concerns proactively. Self-determination theory states that when students feel autonomous and competent in their learning environment, they create a strong sense of academic productivity. According to the social cognitive theory [31], developing self-efficacy through supportive teaching improves learning ability, mediating the beneficial relationship between perceived teaching style and academic resilience [32]. Emotional dysregulation, defined as difficulties in understanding and managing emotions, is a substantial risk factor for adolescents’ mental health concerns [33]. Cyberbullying involves repetitive harassment that can occur anytime, spreading swiftly to a huge audience, with anonymity magnifying its negative effects. Forms include defamation, harassment, and threatening communications, which have psychological and social effects for survivors, such as increased feelings of isolation, anxiety, sadness, and even suicide [34]. Adolescence is a phase marked by turmoil and upheaval, rendering individuals more prone to psychological disorders. These episodes often begin as fleeting but can become enduring, leading to psychiatric conditions, diminished performance, escalated medical expenses, and an elevated risk of subsequent self-harm. Global data indicate that the incidence of online harassment varies between 14.6% and 52%, while rates of being targeted by harmful digital acts range from 6.3% to 32%. The anonymity and widespread nature of cyberbullying can intensify emotional distress, potentially initiating or exacerbating suicides in susceptible youth [35]. Mindfulness significantly mediates the relationship between cyberbullying and cognitive emotion regulation among adolescents.

Resilience theory investigates how people respond positively to adversity, focusing on variables that facilitate recovery from difficult situations. In the context of suicide prevention, resilience refers to protective characteristics that assist individuals in navigating suicidal situations [36]. It includes a positive attributional style and a sense of purpose in life that protect people from suicidality during stressful circumstances [37]. Building resilience includes learning life skills, including problem resolution, emotional regulation, and effective coping mechanisms [38]. By incorporating resilience-building components into this intervention, we want to improve adolescents’ ability to handle stress and minimize their vulnerability to suicidal thoughts and behaviors.

National and international suicide prevention strategies emphasize the significance of schools for targeted efforts [39], as they are conducive and accessible settings for implementing such programs. Leveraging the educational environment effectively enables reach and engagement with adolescents, thereby enabling the provision of relevant support and resources to mitigate the risk of suicidal ideation and behavior. Hence, this study intends to validate and assess the effectiveness of RAAHI (the guide) and a translated and contextualized version, named safeTALK, of the suicide prevention program in GB. Programs such as safeTALK can help lower teenager suicides by teaching them about suicide, giving them the confidence to talk about suicidal feelings, and encouraging them to seek help from professionals such as psychologists or counselors.

There is sufficient evidence that the safeTALK program is efficient and has been implemented in many other countries [29]. This study is the first of its kind in Pakistan to rigorously evaluate the impact of a suicide prevention program. Given the country’s increasing suicide rates and the unique cultural and socioeconomic factors that influence mental health, such as stigma and limited access to services, this research is crucial for addressing a critical public health concern [40]. There is a notable scarcity of culturally adapted, evidence-based suicide prevention programs in Pakistan. Existing interventions often do not consider the unique sociocultural dynamics of Pakistani society, leading to less effective outcomes. Hence, this study aims to evaluate the effectiveness and contextual relevance of suicide prevention programs (RAAHI and safeTALK) in reducing suicidal ideation and enhancing mental well-being among school-going adolescents in GB. In addition, it examines how these programs influence suicide literacy, confidence in discussing suicide, willingness to seek help, mental health outcomes, adaptive coping strategies, and self-efficacy, ensuring their applicability within the local sociocultural context.

### Research Questions

The primary research question about suicidal ideation is as follows: What is the effect of suicide prevention programs (RAAHI and safeTALK) in reducing suicidal ideation among school-going adolescents in GB?

The secondary research question is as follows: What is the effect of suicide prevention programs (RAAHI and safeTALK) among school-going adolescents in GB on (1) perceived suicidal awareness; (2) perceived Social Support Questionnaire; (3) suicide literacy; (4) attitude toward seeking help related to suicidal ideation; (5) life attitude schedule; (6) depression, anxiety, and stress level; (7) adaptive coping strategies; and (8) self-efficacy.

### Null Hypotheses

The hypotheses are as follows:

Hypothesis 1—suicidal ideation risk among school-going adolescents in GB is similar at baseline and 8 weeks following the implementation of the suicide prevention program.Hypothesis 2—Compared to baseline, there is no mean difference in suicide awareness, suicide literacy, and attitude to seek help after 8 weeks of participation in a suicide prevention program (RAAHI and safeTALK) among school-going adolescents.Hypothesis 3—Compared to baseline, there is no difference in the mean score of depression, adaptive coping strategies, and self-efficacy after 8-week suicide prevention programs (RAAHI and safeTALK) among school-going adolescents.

## Methods

The protocol was prepared in accordance with the SPIRIT (Standard Protocol Items: Recommendations for Interventional Trials) guidelines [41]. The trial has been registered in ClinicalTrials.gov (NCT06721364).

### Study Design

This research will use a single-group quasi-experimental pre-post interrupted time-series design to allow for examining any change in the levels of the dependent variables before and after the administration of the intervention [42]. Moreover, there will be no control group, as it would be unethical to withhold intervention from potentially distressed adolescents [42]. The study design allows for assessing intervention effects over multiple time points; it is particularly suitable in settings where randomization is not feasible [43]. To control confounding variables, statistical adjustments and sensitivity analyses will be used to account for potential biases, such as maturation effects and historical events. In addition, the inclusion of multiple assessment points (time point 1, time point 2, and time point 3) strengthens internal validity by capturing trends over time rather than relying on a single before or after measure. By addressing these methodological considerations, we enhance the study’s rigor and reliability.

### Study Phases

This study will be carried out in 2 phases, from January 30, 2024, to October 30, 2025 (Figure 1). Phase 1 will comprise developing the RAAHI intervention by the researcher, followed by translation of the safeTALK intervention module, ensuring its contextualization and validating it through expert review. The effectiveness of the intervention will be evaluated in phase 2 using a quasi-experimental pre-post interrupted time-series design. RAAHI focuses on comprehensive suicide literacy and fostering open discussions to combat stigma about suicide, incorporating wellness education, while safeTALK is a shorter, more targeted workshop teaching specific intervention skills and immediate crisis responses using the tell, ask, listen, and keep safe (TALK) steps to emphasize immediate practical skills for identifying and addressing suicidal behavior by reducing depression and anxiety and improving adaptive coping strategies and the self-efficacy level.

**Figure 1 figure1:**
[figure not shown]
Phases of the study.

### Phase 1

#### Phase 1.1: Development of the RAAHI Module

During phase 1A, an interdisciplinary team comprising mental health nurses, psychologists, and educationists will create the RAAHI module for implementation. The objectives, content, timing, and activities for each module will be designed (Table 1). Experts in the field of mental health will then examine the material for clarity and appropriateness.

**Table 1 table1:** Intervention module objectives and duration.

Session or week and suicide prevention intervention modules		Objectives	Duration (h)	
**RAAHI** **intervention**				3
	Module 1: circle of connection	Establish a warm and inclusive environment through an engaging ice-breaking activity, promoting a sense of connection among participants		
	Module 2: common misconceptions and facts	Establish a warm and inclusive environment through an engaging ice-breaking activity, promoting a sense of connection among participants		
	Module 3: warning signs for suicide	Provide a comprehensive overview of suicide warning signs, empowering participants to recognize and understand these indicators for prompt intervention		
	Module 4: protective factors	Provide a holistic overview of protective factors against suicide, fostering understanding and encouraging the creation of a supportive and nurturing environment		
	Module 5: coping strategies	Offer practical coping strategies, empowering participants with tools to manage negative thoughts, navigate challenges, and build resilience for improved emotional well-being		
**safeTALK intervention**				4
	Module 1: introduction of safeTALK	Establish core beliefs about suicide and its prevention		
	Module 2: importance of safeTALK	Recognize individuals experiencing suicidal thoughts Link individuals with suicidal thoughts to appropriate suicide first aid resources		
	Module 3: Introduce steps of TALK^a^	Present standard procedures for safeTALK, including community and personal reasons, introducing TALK steps, which seek to increase people’s self-awareness and help-seeking behavior while reducing suicidal ideation		

^a^TALK: tell, ask, listen, and keep safe.

#### Phase 1.2: Translation of the safeTALK Intervention Module and Contextual Validation

Translation of the RAAHI and safeTALK intervention material into Urdu, using the backward translation approach, and validation by experts will be carried out to make it culturally and contextually relevant. A team of mental health nurses, clinical psychologists, psychiatrists, and members of the Brain and Mind Institute at the Aga Khan University in Karachi, Pakistan, will validate the intervention module (Table 1).

### Research Setting

GB, located in northern Pakistan, boasts spectacular mountain scenery, as it is spread over a region that has 2 mountain ranges: the Karakoram and the Himalayan. Although the region has great natural beauty, it grapples with poverty, limited mental health services, and harsh living conditions. Efforts to improve well-being in GB require addressing these challenges through initiatives. This study will be conducted in 4 private schools located in northern Pakistan. The rationale for selecting these schools is chiefly the readiness of the school management to implement, adopt, and sustain the intervention. Because this intervention will be used in the Pakistani context for the first time, the willingness of the school principals and their flexibility in mobilizing resources will play a major role. Although the setting will limit external validity, these study sites will be purposively selected, as they will facilitate assessing the feasibility of the intervention in a Pakistani context [44].

### Study Population

#### Inclusion Criteria

Both male and female adolescents enrolled in grades 9 and 10 who can comprehend English and Urdu will be included. In addition, adolescents and their parents must provide consent to participate in the study.

#### Exclusion Criterion

Adolescents who will be absent or sick on the day of data collection and intervention will not be included in the study.

### Sampling Strategy

A multicenter experimental study using consecutive sampling will be conducted to examine the effectiveness of school-based preventive interventions for suicidal behavior. Four schools in the GB regions will be recruited. Eligible schools will be randomly selected. Within the selected schools (clusters), all students in grades 9 and 10 will be invited to participate. This approach of inviting all eligible students within the selected clusters aims to enhance representativeness and minimize potential selection bias that could arise if only specific students were chosen from within each school. This is the best technique to explore the phenomena and to gain rich data from the participants [42]. The chosen design enables the detection of trends and changes over time. This method aids in distinguishing intervention effects from other temporal variables to observe whether changes correlate with the intervention time, which strengthens causal inferences. Multiple assessments establish a baseline trend, differentiating natural development from intervention-induced changes [45]. Regular data collection allows for adjustment of external events influencing outcomes. Despite lacking a control group, this approach enables each participant to serve as their own control, enhancing causal inference [46].

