### Phase 2: Testing the Effectiveness of the Suicide Prevention Program

#### Pretest Phase

Students willing to participate will be asked to provide their consent by signing a form or paper before starting the pen-and-paper pretraining survey. Students will be explicitly informed that participation is entirely voluntary, and their decision to participate or not to participate will not affect their training in any way. First, the psychologist and the researcher will conduct a risk assessment of the students for any previous history or current complaints of suicidal ideation and behavior. A 40- to 60-minute window will be allocated before the training commences to enable participants to complete the pretest survey. In addition, the level of suicide literacy will also be evaluated through validated and self-report questionnaires. Along with this, students’ level of confidence and willingness to discuss suicidal ideation and attitudes toward seeking help from others, adopting coping abilities, and self-efficacy level will also be assessed. Following the pretest phase, the students will enter the intervention phase.

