#### Posttest Phase

The data will be recollected on all outcome measures during posttest phase 1, which is right after the intervention, and posttest phase 2, which will be after 8 weeks of the intervention (Figure 2).

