### Time Frame for Data Collection

Each participant will receive a short questionnaire at 3 points in time: pretest baseline data (T1), immediately after the intervention (T2), and 8 weeks after the intervention (T3). This self-filled questionnaire will collect data on suicidal ideation, level of suicide literacy, level of confidence, and openness to disclose suicidal ideas to others. The researcher will be responsible for checking for and verifying any missing data with participants, which will help to identify and correct errors in the datasets.

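### The study is labelled an interrupted time series but has one pretest and no control group, so the baseline trend and the separation from maturation and history that it claims are not available

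*Protocol article*

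**What the plan says.** **Label.** Study Design in the protocol article describes a "single-group quasi-experimental pre-post interrupted time-series design". The Abstract (Methods) and Study Phases also use the interrupted-time-series label.

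**Claims attached to the label.** Sampling Strategy says: "Multiple assessments establish a baseline trend, differentiating natural development from intervention-induced changes" and "Regular data collection allows for adjustment of external events influencing outcomes". Study Design says that "statistical adjustments and sensitivity analyses will be used to account for potential biases, such as maturation effects and historical events", and that having three time points strengthens internal validity.

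**Assessments planned.** Time Frame for Data Collection lists them all: "pretest baseline data (T1), immediately after the intervention (T2), and 8 weeks after the intervention (T3"). Pretest Phase places T1 just before the training: "A 40- to 60-minute window will be allocated before the training commences to enable participants to complete the pretest survey". Posttest Phase describes "posttest phase 1, which is right after the intervention, and posttest phase 2, which will be after 8 weeks of the intervention".

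**Comparator.** Study Design says "there will be no control group, as it would be unethical to withhold intervention from potentially distressed adolescents".

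**Analysis.** Data Analysis names a linear mixed-effects model for continuous scores, a generalized estimating equation for binary suicidal ideation, and paired t tests and repeated measures ANOVA for suicide literacy. It names no segmented regression and no calendar-time term.

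**Limitation.** Strengths and Limitations accepts that having no suitable control group may weaken internal validity and that some confounders were not fully controlled. The same section calls the pre-post design strong.

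**The concern.** An interrupted time series gets its causal force from the pre-intervention series. That series shows where the outcome was heading, and the post-intervention values are judged against its projection. With one pretest there is nothing to project. The two further assessments both follow the programme, so they describe persistence and not natural development. Using participants as their own controls removes stable differences between people. It does not remove maturation, outside events, repeat testing or regression to the mean.

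At stake is what the trial may conclude. The primary question is the effect on suicidal ideation, and Hypothesis 1 compares baseline with 8 weeks. The Abstract (Objective and Conclusions), Anticipated Findings and Public Health Implications speak of efficacy or effectiveness, and the Abstract and Public Health Implications also look ahead to scale-up. If the text says that natural change has been separated out, a reader will take any T1-to-T3 change as caused by the programme.

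**Working it through.** **1. Count the assessments.** Before the programme: 1 (T1). After it: 2 (T2, T3). Concurrent untreated groups: 0.

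**2. Write the model that the label implies.** Segmented regression has four mean parameters: baseline level *a*, pre-intervention slope *b* per week, level change *L*, and slope change *S*. Put T1 at week 0, T2 at week *g* (just after the workshops; the exact gap is not stated), and T3 at week *g* + 8. With the interruption placed at T2:

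- mean at T1 = a
- mean at T2 = a + b·g + L
- mean at T3 = a + b·(g + 8) + L + 8·S

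This gives three means for four parameters. For any *g* > 0 the design matrix has rank 3 of 4, and *b*, *L* and *S* are each not estimable. More participants do not help, because everyone has the same three occasions.

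**3. See what each contrast contains.**

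- T2 − T1 = L + b·g. If *g* is short, the drift term b·g is small. The main concern for this contrast is then testing and demand effects, which are part of the observed change and cannot be told apart from *L*.
- T3 − T1 = (L + 8·S) + b·(g + 8). The programme effect at 8 weeks comes with at least 8 weeks of drift. This is the Hypothesis 1 interval.
- T3 − T2 = 8·(b + S). This slope equals the natural slope only if S = 0, which the data cannot test.

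**4. Check what would change this.** A second pretest *h* weeks before T1 adds T1 − T0 = b·h, which gives *b*. The rank becomes 4 of 4 with 2 pre and 2 post assessments. That is the bare minimum, since two points cannot show whether the baseline trend is linear. With 3 pre and 2 post the rank is again 4, with one time point to spare.

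**5. Illustrate the consequence.** The drift sizes are assumptions; the article gives none.

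- Completers: 267 × 0.8 = 213.6, taken as 213 (sample size and 20% dropout from Sample Size).
- Test: paired t, two-sided 0.05, on a continuous score. The critical value on 212 degrees of freedom is 1.971.
- Noncentrality = d × √213 = 14.595 × d, where *d* is the drift in SDs of the change score and the true programme effect is zero.

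| Assumed drift *d* | Noncentrality | Probability of a significant result |
|---|---|---|
| 0.1 | 1.459 | 0.31 |
| 0.2 | 2.919 | 0.83 |
| 0.3 | 4.378 | 0.99 |

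With the article's own required number of 223 instead of 213, √223 = 14.933. The noncentralities are then 1.493, 2.987 and 4.480, and the probabilities 0.32, 0.84 and 0.99, so the choice between the two numbers hardly matters.

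**The case against.** The strongest reply has four parts.

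**The weakness is disclosed.** Study Design already says single-group and pre-post and gives an ethical reason for having no control. The null hypotheses are worded as change from baseline, and Strengths and Limitations concedes the threat to internal validity. This stands as far as it goes: the missing control group is a declared choice and is not the error. But the concession does not withdraw the baseline-trend and adjustment claims. Study Design and Sampling Strategy therefore contradict Strengths and Limitations.

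**Time and exposure are not the same on every scale.** A reader might infer that no analysis could separate any time-related influence from the programme. The article does not support that for calendar time. Intervention puts about 30 students in each workshop, four schools take part, and Projected Timeline spreads delivery over July and August 2025. If groups are tested and trained on different dates, events tied to the calendar could be partly separated across groups, under assumptions. No such analysis is stated, so this narrows the point without rescuing the text. Maturation and repeat testing, which run on each student's own study time, stay inseparable.

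**The probabilities do not measure bias.** A reader might take 0.83 as this trial's false-positive rate. It is not. It shows only that about 200 pairs detect small changes, and nothing in the article says how much drift to expect. The calculation also uses a paired t test, whereas binary suicidal ideation is planned as a generalized estimating equation. This stands, so the figures are illustration only.

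**Misreporting is a prediction.** A reader might infer that any significant change will certainly be published as efficacy. The efficacy and effectiveness wording makes that plausible but does not establish it.

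**Conclusion.** The concern holds as a wrong statement about the design. One pretest, two posttests and no control group cannot yield a baseline trend, a level change or a slope change. The promised adjustment for maturation has nothing to identify it, and no planned comparison supports the adjustment for historical events. These conclusions follow from the count of assessments and need no numerical assumption. They are not details that an analysis plan could supply, because the number and timing of assessments are fixed here.

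The weight differs by contrast: greatest for T1 to 8 weeks, and mainly testing and demand effects for T1 to T2. The size of any bias is unknown. The probabilities of 0.31, 0.83 and 0.99 rest on assumed drifts, 213 completers and a continuous score. The documents do not support the broader reading that the study is uninformative: it can estimate change from baseline and whether that change persists to 8 weeks.

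**What to change.** **Needed (wording only).**

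- Describe the study as a single-group pre-post study with three measurements. Remove the interrupted-time-series label from the Abstract (Methods), Study Design and Study Phases.
- Delete the baseline-trend and external-event claims in Sampling Strategy and the maturation and history claims in Study Design. Bring both sections into line with Strengths and Limitations.
- Word conclusions as change from baseline, not as efficacy or effectiveness, in the Abstract (Objective and Conclusions), Anticipated Findings and Public Health Implications.

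This can be done at any stage and is sufficient alone.

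**Optional, only if workshops have not yet been delivered and the timeline allows.** Take T1 in all groups at the start, order the workshop dates at random, and repeat the pretest in later groups just before their workshop. Their change between the two pretests estimates untreated drift.

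This costs one extra questionnaire for about half of the students and a randomly ordered calendar. Its limits are:

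- few groups (267 / 30 = 8.9, about nine), so the comparison is imprecise;
- possible contamination within schools;
- delay for some students, which has to be weighed against the ethical reason given in Study Design.

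Feasibility is uncertain. The Abstract (Results) has data collection starting in March 2025 and 267 recruited by April 2025. Study Progress to Date has recruitment commencing fully in August 2025, and Projected Timeline has delivery in July and August. Eight weeks after a late-August workshop is late October, against a study end of October 30, 2025 in Study Phases. These dates must be reconciled before the option is considered.
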